## Abstract

**Introduction:**

Coronary heart disease is becoming more common in developing nations. Acute coronary syndrome (ACS) poses a major challenge to global health; however, access to cardiac rehabilitation and preventative measures is limited. There is an urgent need for affordable and widely accessible alternative delivery models to resolve this treatment gap. Research conducted by both local and international experts has focused on the role of smartphones in offering rehabilitation guidance and secondary prevention for patients. Rehabilitative effects have mainly been observed in areas where risk factors and behavioural adjustments can be altered. However, high-quality, evidence-based randomized controlled trials (RCTs) are lacking. Furthermore, the previous studies were single-centre studies with restricted case sources, thereby leading to relatively weak external validity of the research findings. Additionally, most of the previous studies have evaluated cardiac function indicators, with limited assessments of patients' clinical endpoint indicators, quality of life, and psychological aspects.

**Method and analysis:**

The purpose of this study is to explore the development of a smartphone-based systematic and extensible digital management model for post-percutaneous coronary intervention (PCI) outpatient care among ACS patients. We aim to assess whether the integration of a digital management model with conventional postoperative follow-up management is more beneficial for patient recovery during the outpatient rehabilitation process than conventional postoperative follow-up management alone. We propose a single-blind, multicentre RCT of 1,366 ACS patients who underwent PCI and who completed 12 months of follow-up. In the experimental group, within one year after discharge, participants will receive both the current standard postoperative follow-up management and additional management via a digital platform. In the control group, within one year after discharge, participants will receive only the current standard postoperative follow-up management. The primary clinical endpoint of this study is major adverse cardiovascular and cerebrovascular events (MACCEs), whereas the secondary clinical endpoints include cardiac function indicators, quality of life scores, and mental health scores, among other endpoints.

**Conclusions:**

This clinical trial will provide evidence to demonstrate whether digital health management is a better approach for improving clinical outcomes in patients with post-PCI ACS.If proven effective, this digital model could address the global underutilization of cardiac rehabilitation by providing scalable, low-cost solutions, particularly in rural and resource-limited settings. Clinically, it may reduce MACCEs and improve quality of life, while public health systems could integrate this approach to alleviate workforce shortages and geographic barriers.

**Trial Registration Number:**

https://www.clinicaltrial.gov, identifier ChiCTR2400086452.

## Introduction

Acute coronary syndrome (ACS), which is a significant cause of cardiovascular disease-related deaths worldwide, is a sudden heart condition caused by the rupture or erosion of unstable atherosclerotic plaques in the coronary arteries. This event is followed by the formation of new thrombi (1). The frequency of cardiovascular diseases in China is currently increasing on a yearly basis, and cardiovascular disease-related deaths have become one of the major causes of total deaths among both urban and rural residents (2). The use of percutaneous coronary intervention (PCI) has considerably decreased the death rate in patients with ACS (3). However, patients still experience adverse cardiac events such as cardiac insufficiency, myocardial remodelling, recurrent refractory angina, repeat revascularization, and cardiac death (4), which significantly impact the overall prognosis and quality of life of patients with ACS. Therefore, PCI is not a one-time solution, and numerous issues remain to be addressed after PCI. Consequently, effective cardiac rehabilitation and secondary prevention (CR/SP) for patients after PCI are particularly important.

Currently, multiple studies (5, 6) have confirmed that standardized CR/SP for patients who undergo PCI can effectively control risk factors for cardiovascular diseases, enhance adherence to cardioprotective medications, improve patients' quality of life, and enhance postcardiovascular event prognosis. Specifically, this approach can reduce cardiovascular mortality by 26% and hospitalization rates by 18%. Mampuya Wamer M (7) proposed that cardiac rehabilitation can decrease mortality, alleviate symptoms, promote smoking cessation and alcohol restriction, improve exercise tolerance, and control risk factors; however, they also noted that the effectiveness of cardiac rehabilitation is limited by issues such as referral problems and poor registration. Lv et al. (8) implemented continued management for PCI patients through an out-of-hospital PCI club, which improved patients' adherence to medical advice, effectively controlled the risk factors for coronary heart disease, reduced cardiovascular events, and facilitated postoperative recovery. Sora Baek et al. (9) conducted educational courses and cardiac rehabilitation training for patients residing in rural areas within the community. The results revealed significant reductions in patient weight and blood glucose levels, as well as improvements in the 6-minute walk test (6MWT) results, thereby confirming the effectiveness of this community-based cardiac rehabilitation management model. Thus, standardized management of cardiac rehabilitation for patients who undergo PCI is particularly important, as this management approach can improve patients' cardiac rehabilitation levels and further enhance their quality of life.

However, CR/SP services are still not fully utilized on a global scale, despite the recognized benefits. Therefore, innovative strategies are needed to implement evidence-based treatments. The CR/SP model should be accessible, affordable, and scalable to effectively treat coronary heart disease and resolve the gap between existing practices and recommended guidelines (10). With the rapid advancement of the internet and the growing variety of communication techniques, smartphone-based programs have demonstrated effectiveness as being alternative methods for delivering rehabilitation and secondary prevention to patients with coronary heart disease; this is especially true for the alteration of risk factors and changes in behaviour. In China, the rapid growth of smartphone and social media users has led to the formation of an effective platform for offering CR/SP services through these media. To date, research reports from both domestic and international sources have examined the application of smartphones for providing rehabilitation guidance and secondary prevention for patients (11, 12). Notably, implementation studies in Europe have demonstrated the clinical viability of mHealth platforms for coordinating secondary prevention strategies in post-myocardial infarction populations, particularly through structured remote follow-up systems (13). Mobile apps technology can be used as a safe choice to improve the health status and enhance physical vitality of elderly patients with coronary heart disease (14). In the study by Effie et al. (15), an internet- and mobile phone-based management model was found to effectively improve patients' cardiac rehabilitation outcomes and enhance their adherence. With particular respect to patients in rural areas, this internet-based management model provides considerable convenience, thus effectively addressing the issue of inaccessible medical care due to their remote locations. In the study by Pemille Lunde (16), the significant role of mobile applications in patients' cardiac exercise rehabilitation and the control of cardiovascular disease risk factors was fully demonstrated. Tashi Dorje et al. (11) used the SMART-CR/SP system via smartphone WeChat software to provide at-home cardiac rehabilitation and secondary prevention initiatives for post-PCI coronary heart disease patients. The results showed that the use of the SMART-CR/SP system could significantly improve patients' post-PCI cardiac functional capacity, blood pressure control, medication adherence, and knowledge regarding lipids and coronary heart disease. Mobile applications, which have the advantages of high accessibility, opportunities for two-way communication, and the ability to exchange information in real-time, serve as significant assets for disease prevention and management methods, including mass public health education, personalized healthcare, and customized treatment.

When considering the somewhat restricted number of clinical studies focusing on the success of internet- and smartphone-based outpatient rehabilitation management for post-PCI ACS patients, as well as the lack of large-sample, multicentre RCTs, the case sources are somewhat restricted, and the generalizability of the research findings is weak.

Therefore, the aim of this study is to conduct a multicentre RCT in China. Additionally, previous clinical assessments have primarily focused on patients' cardiac function indicators, whereby they often used the 6-minute walk distance as the main outcome measure, with limited research on clinical endpoint indicators such as major adverse cardiovascular and cerebrovascular events (MACCEs), patients' quality of life, mental health, and other cardiac function indicators (such as brain natriuretic peptide). Therefore, in this study, in addition to focusing on the 6-minute walk distance as a cardiac function indicator, we will also assess MACCEs, quality of life, and other cardiac function evaluation indicators within and between groups to better understand the impacts of digital health management on the outpatient rehabilitation effect for ACS patients who undergo PCI. These findings will provide a basis for an accessible, affordable, and scalable CR/SP model and provide the foundation for improvements in home-based rehabilitation management.

## Methods and analysis

### Study hypotheses

The purpose of this trial is to test the hypothesis that a digital health management model that combines smartphone applications with the current routine postoperative follow-up management model is superior to the current routine postoperative follow-up management model alone for the outpatient rehabilitation of patients with ACS who underwent PCI.

### Study design

This study will be a multicentre, open-label, endpoint-blinded RCT. The trial will be conducted at 9 medical centres in China and will include 1,366 patients. The flowchart of the study process is shown in Figure 1.

**Figure 1 F1:**
[figure not shown]
Flowchart of the clinical trial design.

This clinical trial will adhere to the principles outlined in the Declaration of Helsinki. The Clinical Trial Ethics Committee of The First Affiliated Hospital of Xi'an Jiaotong University, as well as each medical centre, reviewed and approved the clinical trial protocol and informed consent documents. All of the patients participating in the study must provide written informed consent. The study protocol is registered with the China Clinical Trial Registry (ChiCTR2400086452).

### Study population and randomization

A total of 1,366 ACS patients who underwent PCI and who meet the inclusion criteria without meeting any exclusion criteria will be included from nine research centres. The allocation of patients will be randomized via an interactive web randomization system.

### Inclusion criteria

a.Participants aged between 18 and 70 years;b.Newly diagnosed patients meeting the clinical diagnostic criteria for ACS (17);c.Individuals who have undergone PCI and subsequently met the criteria for hospital discharge;d.Patients with an anticipated survival duration exceeding one year;e.Patients who possess adequate learning, comprehension, and communication abilities, thus enabling them to grasp the pertinent aspects of the trial and actively collaborate with research requirements;f.Participants who are proficient in smartphone usage, capable of operating specialized “Jiuyi” software, and expressing interest in participation;g.Patients with comprehensive clinical records who voluntarily elect to participate, have obtained familial consent, and are amenable to signing the informed consent form.

### Exclusion criteria

a.Individuals presenting with severe cardiac, hepatic, or renal dysfunction, immune system disorders, or any other acute or chronic severe systemic illnesses;b.Patients who suffer severe complications, including dissection, shock, or substantial haematoma, after PCI;c.Patients diagnosed with haemorrhagic diseases or malignant tumours;d.Patients with untreated ventricular tachycardia, advanced heart failure, intractable hypertension, or hypotension;e.Individuals with a prior history of cardiac surgical intervention;f.Patients affected by mental illness, profound cognitive impairments, or an absence of autonomous behavioural capacity;g.Participants unable to use a smartphone for the duration of the trial due to visual, auditory, or motor impairments;h.Residents in locations lacking internet access;i.Patients declining to provide written informed consent.

### Study procedures

This study will adopt a stratified block randomization approach.
(1)First, patients will be stratified based on their GRACE scores.For GRACE scores, with respect to the postdischarge patients, the low-risk category will consist of patients with scores up to 88, the moderate-risk category will consist of those scoring between 89 and 118, and the high-risk category will consist of patients scoring greater than 118. Patients in the low-risk category will have a score of 108 or less, those in the moderate-risk category will have scores ranging from 109–140, and patients in the high-risk category will have scores greater than 140.
Randomization will be stratified by GRACE risk score (low, moderate, high) and center. Blocks of 4 patients within each stratum will be randomized 1:1 using a web-based system (Sealed Envelope™), ensuring allocation concealment.(2) Block randomization within strataRandomization within strata will be achieved via block randomization as follows.
(1)Numbering: Patients will be numbered on the basis of the order of their enrolment within each stratum. For example, the first high-risk patient will be labelled H001, the first moderate-risk patient will be labelled M001, and the first low-risk patient will be labelled L001, thereby generating continuous ID numbers within each stratum.(2)Block formation: Every four consecutively enrolled patients within each stratum will be grouped into one block; thus, each block will include four patients.(3)Randomization: A seed number will be established, and four random numbers corresponding to the IDs will be generated within each block. The four subjects within each block will then be ranked according to the random numbers. The top two subjects in each block will be assigned to the experimental group, whereas the bottom two subjects will be assigned to the control group. The allocation results will be sorted in ascending order by ID number to form a randomization table within each stratum.
(3)Patient groupingResearchers at each centre will obtain randomization information for patients from a designated person based on the randomization table and the order of patient enrolment. The participants will be equally divided between the experimental group and the control group.

Experimental Group: Within one year after discharge, patients will receive digital platform management in addition to the current standard postoperative follow-up management.

Control Group: Within one year after discharge, patients will receive the current standard postoperative follow-up management.

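### Fixed, published blocks of four within centre strata of an open-label trial let about one third of allocations be deduced, so the concealment claim is too strong

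*Protocol article*

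**What the plan says.** All references are to the protocol article.

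- **Block size (Study procedures).** The section first says: "Blocks of 4 patients within each stratum will be randomized 1:1 using a web-based system". Its later account of how blocks are formed repeats the size: "Every four consecutively enrolled patients within each stratum will be grouped into one block; thus, each block will include four patients". The size is constant, and no sentence says that it varies or is kept from the centres.
- **Balance within the block (same section).** "The top two subjects in each block will be assigned to the experimental group, whereas the bottom two subjects will be assigned to the control" arm. Every block is therefore exactly 2:2.
- **Strata (same section).** "Randomization will be stratified by GRACE risk score (low, moderate, high) and center".
- **Concealment (same section).** Patients are to be "randomized 1:1 using a web-based system (Sealed Envelope™), ensuring allocation concealment".
- **How a centre learns the allocation (same section).** After naming the web system, the section describes a randomisation table drawn up in ID order and a designated person who passes allocations to each centre's researchers as patients enrol. IDs run consecutively within stratum; the examples are H001, M001 and L001.
- **Masking (Study design).** "This study will be a multicentre, open-label, endpoint-blinded RCT".
- **Centres and sample size (same section).** "The trial will be conducted at 9 medical centres in China and will include 1,366 patients".
- **Status (Trial status).** Recruitment is in progress at the nine centres.

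**The concern.** A web system hides the list. It cannot hide an allocation that follows by subtraction. With a known block of four, the fourth allocation is always fixed by the first three, and the third is fixed whenever the first two agree. In an open-label trial stratified by centre, staff can see every earlier allocation in their own stratum, and consecutive IDs show where the next patient sits in the block.

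Foreknowledge matters because it allows a patient to be enrolled, deferred or passed over according to the arm that is due. The Inclusion criteria leave some room for this: they ask for adequate learning, comprehension and communication ability and for proficiency with a smartphone, both matters of judgement. Another condition, "expressing interest in participation", is the patient's own act, but the way the trial is presented may influence it. Selection of this kind happens before randomisation. Blinded endpoint assessment comes later and cannot undo it, and covariate adjustment repairs it only for the characteristics that are measured.

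**Working it through.** **Inputs from the article.** Block size 4, 2:2; 3 GRACE categories × 9 centres = 27 strata; 1,366 patients, so 1,366 / 27 = about 51 per stratum on average. The article gives no figure for predictability, so there is none to reproduce.

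**1. Share of allocations that can be deduced, complete blocks.** A 2:2 block of four has 6 equally likely sequences (E = experimental, C = control).

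| Sequences | Number | Positions fixed by earlier ones |
|---|---|---|
| EECC, CCEE | 2 | third and fourth (2) |
| ECEC, ECCE, CEEC, CECE | 4 | fourth only (1) |

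Expected number per block = (2 × 2 + 4 × 1) / 6 = 1.333, and 1.333 / 4 = 33.3%. By position the probabilities are 0, 0, 1/3 and 1. Applied to everyone: 1,366 / 3 = 455.

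**2. Incomplete last blocks.** In a stratum of 50 there are 12 full blocks and 2 patients over: 12 × 1.333 = 16, and 16 / 50 = 32.0%, or about 437 of 1,366. Simulating 1,366 patients spread at random over 27 strata gives 32.5%, or about 444, with equal or unequal strata. About 32%, roughly 440 patients, is a fair summary.

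**3. Best guess.** Always guessing the arm that is behind in the block succeeds (0.5 + 0.667 + 0.667 + 1) / 4 = 70.8% of the time in complete blocks. In a stratum of 50 it is (12 × 2.833 + 1.167) / 50 = 70.3%. Chance is 50%.

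**4. If blocks ran across centres within GRACE category.** Assume nine equal centres, each seeing only its own allocations but knowing its position in the block from the ID. An allocation can be deduced only if the two earlier patients who fix it were at the same centre, which has probability (1/9)² = 1/81. The share is 1/3 × 1/81 = 0.4%. For a centre with share w of recruitment it is w²/3 of that centre's own patients, so large centres would be somewhat higher.

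**5. Effect of varying the block size.** Simulated strata of 50, with staff assumed to know the set of sizes but not their order:

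| Block sizes | Certain allocations | Best-guess success |
|---|---|---|
| 4, fixed | 32% | 70% |
| 4, 6 | 5.6% | – |
| 2, 4, 6 | 4.0% | – |
| 4, 6, 8 | 2.3% | 68% |

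A larger fixed block of known size helps much less: 25% certain for size 6 and 20% for size 8 (complete blocks).

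**6. Power if deducible allocations are left out.** The article's formula with 20% and 14% gives 2 × 0.17 × 0.83 × (1.96 + 0.84)² / 0.06² = 614.6, so 615 per group, as stated. Dropping one third leaves 615 × 2/3 = 410 per group. Then Zβ = √(410 × 0.0036 / 0.2822) − 1.96 = 2.287 − 1.96 = 0.327, a power of about 63%.

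**The case against.** Three objections deserve weight.

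**Deducible is not the same as known.** A reader might infer that site staff know a third of allocations in advance, or that concealment is absent altogether. The documents support neither. They do not show that anyone tracks allocations or acts on them, and the list itself may be well hidden. This stands: the weakness is an opening, affecting about a third of patients.

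**Blocks may not run within centre.** The same section begins by stratifying on GRACE alone, and its example IDs carry no centre code. If that is how the table was built, a site could deduce about 0.4% with equal centres, and the concern largely disappears. This stands as a condition. However, the article expressly names centre as a stratification factor; if that is not what is done, the sentence needs correcting.

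**The harm cannot be put in numbers.** One might multiply the deducible share by a rate of exploitation and a risk difference, and set the result against the planned 6-point effect. Neither input is in the documents, and plausible choices run from negligible to material. No such figure should be used.

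A condensed article may also leave operational safeguards to the full protocol. That excuses missing detail. It does not cover a fixed block size that the article itself publishes alongside an assurance of concealment.

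**Conclusion.** The point holds in a conditional form. As written, the design lets site staff who follow their own stratum deduce 33.3% of allocations in complete blocks, about 32% or roughly 440 of 1,366 overall. The assurance of concealment therefore claims more than the procedure delivers. The conclusion rests on four statements in the article: constant blocks of four split 2:2, centre as a stratum, open-label treatment, and recruitment continuing after the block size was published.

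The one-third figure is exact arithmetic; confidence is lower on whether blocks really run within centre. Whether any selection has occurred, and how large a bias would follow, cannot be determined from the documents. The planned sample size is not affected. This should be corrected while patients remain to be enrolled, but it does not invalidate the trial.

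**What to change.** For the patients still to be randomised:

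1. **Vary the blocks.** Have the web system generate blocks of random size (for example 4, 6 and 8) within each centre-by-GRACE stratum, and keep the sizes in a document that centres do not see. Certain allocations fall to about 2%. Best-guess success falls only from about 70% to 68%, so the gain lies in removing certainty and some guessing remains possible.
2. **Use one route.** Reconcile the web system with the designated person and the pre-made table, so that a single central, concealed route issues allocations. Without this, a configuration change in the web system may not reach the mechanism actually in use.
3. **Correct the text.** State whether blocks run within centre, bring the ID scheme into line with that, and replace the assurance of concealment with a description of the process.
4. **Supportive analysis only.** An analysis that omits allocations already fixed by earlier ones in their block may be reported. If the whole trial had used fixed blocks it would drop about a third of patients, with power of about 63% under the protocol's assumptions, and it cannot remove bias from allocations that were guessed correctly without being certain. It should not replace the primary analysis.

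The cost is a configuration change, a short amendment, and a largest end-of-stratum imbalance of 4 patients instead of 2, which is small against an average of about 51 per stratum.

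### A fixed, published block size of 4 in an open-label trial still recruiting lets up to one third of allocations be deduced under centre-by-GRACE strata, and the table-and-designated-person route is not reconciled with the web system

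*Protocol article*

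**What the plan says.** **Block size and strata.** Under Study procedures, the protocol article says "Randomization will be stratified by GRACE risk score (low, moderate, high) and center". Nine centres and three classes give 27 strata. It then says "Every four consecutively enrolled patients within each stratum will be grouped into one block; thus, each block will include four patients", with two patients per arm in every block: "The top two subjects in each block will be assigned to the experimental group, whereas the bottom two subjects will be assigned to the control".

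**Web route.** Study population and randomization says "The allocation of patients will be randomized via an interactive web randomization system". Study procedures repeats this: "Blocks of 4 patients within each stratum will be randomized 1:1 using a web-based system (Sealed Envelope™), ensuring allocation concealment".

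**Table route.** Later in Study procedures, a seed generates random numbers, and the sorted results form a randomization table for each stratum. Under the patient-grouping item, researchers at each centre "will obtain randomization information for patients from a designated person based on the randomization table" and the order of enrolment. The illustrative labels carry a GRACE letter and no centre code: "the first high-risk patient will be labelled H001, the first moderate-risk patient will be labelled M001, and the first low-risk patient will be labelled L001".

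**Setting.** Study design describes a "multicentre, open-label, endpoint-blinded RCT". Trial status says that the nine centres are still recruiting.

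**The concern.** In an open-label trial, site staff see each allocation once it is made. If they also know that every block holds two patients per arm, they can work out the end of a block from what has gone before. The block size is in print while patients are still being enrolled.

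This matters because eligibility leaves room for judgement: comprehension, smartphone skill and interest in taking part, expected survival beyond one year, and whether organ dysfunction counts as severe. A recruiter who knows the next arm could approach or pass over a patient according to prognosis. Blinded endpoint assessment does not correct selection at entry, so any such selection would carry into the MACCE comparison.

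The second difficulty is that the article credits concealment to a web system and then describes allocations reaching the centres by another route. The reader cannot tell which one protects the sequence.

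**Working it through.** The article states no predictability figure, so there is none to reproduce.

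**Inputs.** Block size 4, two per arm; strata of GRACE (3) by centre (9); N = 1,366; open-label; recruitment ongoing. All come from Study design, Study procedures and Trial status. Assumptions: the recruiter knows every earlier allocation in the stratum and where blocks begin, and strata are of equal size.

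**1. Complete blocks, centre-by-GRACE strata.** An allocation is certain once one arm's two places are used. There are six equally likely orders.
- AABB and BBAA reveal positions 3 and 4, two allocations each.
- The other four orders reveal position 4 only.
- Expected number certain per block = (2×2 + 4×1)/6 = 8/6 = 1.333. Share = 1.333/4 = 33.3%.
- By position, the probability of certainty is 0, 0, 1/3, 1.
- If all blocks were complete: 1,366/3 ≈ 455 allocations.

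**2. Incomplete last block.** 1,366/27 ≈ 50.6 patients per stratum. With 50 patients there are 12 full blocks plus two patients, for whom nothing is certain: 12 × 1.333/50 = 16/50 = 32.0%. Simulation of 4,000 strata of 50 also gave 32.0%.

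**3. Best guess.** Guessing the arm that is behind, and tossing a coin when level, is right with probability 1/2, 2/3, 2/3 and 1 at positions 1 to 4. The mean is 2.833/4 = 17/24 = 70.8%, against 50% under simple randomization. It is 70.3% with 50 patients per stratum.

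**4. GRACE-only sequences shared by nine equal centres.** Suppose a centre sees only its own allocations but knows block positions from the ID numbers.
- Position 3 is certain if both earlier patients came from that centre (1/81) and had the same arm (1/3): 1/243.
- At position 4, two of the three earlier patients share an arm. The allocation is certain if both came from that centre: 1/81 = 3/243.
- Average over four positions: (1/243 + 3/243)/4 = 1/243 ≈ 0.4%. Simulation gave 0.41%.

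**5. Randomly varying block sizes.** Simulation in strata of 50, conservatively letting the recruiter know the set of sizes and all earlier allocations. The sets are illustrations only.

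| Block sizes | Known for certain | Best guess right |
|---|---|---|
| 4, fixed | 32.0% | 70.3% |
| 2, 4, 6 | 4.1% | 70.0% |
| 4, 6 | 5.7% | 69.0% |
| 4, 6, 8 | 2.2% | 67.7% |

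Varying the sizes removes most of the certainty and very little of the guessing advantage.

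**6. The two routes side by side.** A web system that issues each allocation at enrolment needs no person to read from a table. The table text could describe how the list was generated before being loaded into the web system. The designated-person step does not fit that reading, because it says that centre researchers get allocations from that person. The article does not connect the two.

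**The case against.** A fixed block of four is common and is not an error in itself. The one-third figure needs centre-specific strata and a recruiter who tracks everything; on the GRACE-only reading it nearly vanishes. Both points stand, so one third is an upper bound and not the share that is known.

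A reader might infer more than the article supports:
- **That concealment is absent or has failed.** A web system that releases a code at enrolment does hide the next code. Deducing it from past open allocations is predictability, a separate matter. Nothing in the article shows a breach.
- **That the designated person exposes the sequence.** A central holder who is independent of recruitment is an accepted method. The article does not say that this person recruits, and custody of the list may be covered in the full protocol.
- **That the table route leaves centre unbalanced.** The labels are given as an example, and the preceding paragraph defines strata by GRACE and centre. A missing centre code does not establish three shared sequences.
- **That the guess rate of about 71% is harm the change would remove.** It stays near 70%, since it comes from small balanced blocks generally.

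The size and direction of any bias on MACCE cannot be derived from the article. What remains is avoidable predictability under the stratification stated, and two allocation routes that the text leaves unreconciled.

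**Conclusion.** The point holds with conditions. Under the stated centre-by-GRACE strata, a recruiter who knows all earlier allocations and the block boundaries could know up to 33% of allocations in advance, or about 32% with about 51 patients per stratum. Under GRACE-only sequences shared by nine equal centres, a single centre acting alone could know about 0.4%. Unequal centres would shift these figures, but one third remains the ceiling for deduction from past allocations.

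Separately, the article attributes concealment to a web system yet describes a table and a designated person. Protection against selection at entry is therefore not assured; it has not been shown to be broken. Confidence is high for the arithmetic and for the textual inconsistency. No claim is made that selection has occurred. The change is worth making because recruitment is open and the remaining allocations can still be protected.

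**What to change.** For all remaining patients:
- Allocate only through the central web system, stratified by centre and one GRACE classification. Study procedures gives two sets of cut-offs (88/118 and 108/140), which must be reconciled so that each patient falls in one stratum.
- Use randomly varying block sizes. Do not disclose the values to sites, and do not print them in the amendment or elsewhere until recruitment ends.
- Remove the designated-person and table text, or state how it relates to the web system. Say whether sequences are centre-specific.

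For patients already enrolled, report which procedure was used.

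The cost is an amendment and a settings change in the existing web system. Sample size is unaffected. The downside is slightly larger possible imbalance in small strata. The gain is limited to certain knowledge, which falls from about 32% to a few percent; best-guess accuracy stays at about 70%.
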